### Trial management and quality assurance

A CRA will perform regular monitoring sessions and interim analyses every 6 months (independent from study investigators and sponsor), in which protocol compliance and correctness of data will be assessed. The CRA will have direct access to medical records, radiographic images, the hospital information system, and all study material for source data verification, will report all serious adverse events (SAEs) to the institutional ethics committee in accordance with all legal and institutional requirements. Case report forms (CRFs) will be generated and stored at the study site. Adherence to the follow-up investigation schedule will be promoted by mailing reminders to the patient 1 month in advance. In addition, the CRA will perform continuous monitoring for adverse events during the study period using the above-mentioned resources and report adverse events and other unintended effects of trial interventions or trial conduct to the institutional ethics committee, which under applicable law has the authority to terminate the trial. Potential relevant protocol modifications must be communicated to the ethics committee and will be communicated to this journal. Confidentiality of personal information will be provided by (a) keeping all documents containing personalized information strictly on site and accessible only by authorized personnel bound by written obligation to confidentiality, (b) anonymizing patient data in the CRFs and the data analysis files. All authors will have unlimited access to the final trial dataset and did not enter agreements that limit such access. Additional file 2 shows the SPIRIT 2013 Checklist as recommended for clinical trial protocols.

## Discussion

The present study is challenging in that it compares two different self-expanding nitinol-stents head-to-head against each other. Very few studies have been successful in this respect, and there are ongoing studies facing this challenge [20], where it remains to be seen whether their sample size calculation can stand up to reality. Consequently, there are currently no prospective studies comparing self-expanding stents with different COF.

The authors believe that in such studies (where a binary endpoint event occurs quite infrequently and in a very similar proportion of patients in either group), binary endpoints do not provide enough power for successful completion without demanding unreasonably high patient numbers. To optimize the power of this study, we dropped both clinical TLR and binary re-stenosis at color-flow Doppler ultrasound (CDUS) as primary endpoints. TLR is a parameter prone to bias, especially if the study team themselves schedule patients for re-intervention, and in claudicants it is further biased on purely subjective estimations by the patient (pain) and by the physician (urgency and resource availability). CDUS is in addition highly operator- and patient-dependent and both parameters are only binary. We selected as outcome parameter the amount of neointima inside the stent accessed by CT angiography. Neointimal volume is calculated based on 20 to 160 individual levels (depending on total stent length every 2 mm along the stent longitudinal access), with each level consisting of four individual measurements (stent diameter in two directions, lumen diameter in two directions). By using the difference between the stent diameter and lumen diameter in a multitude of data points, normal distributions of the results even from skewed data is likely, and the accuracy of the end result as the average of n independent measurements will (theoretically) be improved over the native resolution of a single CT measurement by a factor of √n. Furthermore, in-stent neointima can be detected with CT angiography in virtually every patient after 1 year post implantation, since the detection threshold of the CT is estimated to be at 0.5 mm of luminal narrowing.

A further advantage of CTA assessment of in-stent neointima is the option to locally compare different areas of COF (e.g., in places where some residual stenosis leads to higher compression of the stent and thus to higher chronic outward force, while in other regions where the stent is near its nominal diameter COF might be locally low). The stent diameter (and COF), as well as the amount of neointima, is known every 2 mm along the stent longitudinal access, therefore in-group and in-patient correlations of COF and neointima are possible in post hoc evaluations. If neointima formation is highest at the very same location as high COF, a direct activation of muscle cell proliferation may be assumed. Conversely, if neointima formation occurred downstream from areas with high COF, humoral or paracrine stimulations might be possible.

The study differs further from some similar previous trials in its generous inclusions criteria. Claudicants, patients with tissue loss, as well as diabetic patients are included; inflow and outflow lesion treatment is permissible, TASC A-D lesions are included. This was done in effort to perform the trial on a patient sample that closely represents real-world patients of a specialized endovascular center. The authors believe that it makes little sense to perform trials only on a highly selected collective of participants (representing possibly 1% of all patients) if then (as it is often the case) the conclusions drawn from such selective cohorts are then only generalized to the public anyway.

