**Fig. 4 Fig4:**
[figure not shown]
Chronic outward force of different stent fabricates according to stent diameter

The two stent choices were based on bench test data provided by Biotronik AG on SFA stents from various manufacturers. Using these curves, the COF of each stent can be determined for every diameter below its nominal diameter. The LifeStent shows the steepest COF curve, while the AstronPulsar stent shows the flattest curve. When comparing both stents at a size of 6 × 100 mm the mean values for maximum and minimum RRF are lower for the Pulsar-18 compared to the LifeStent (0.464 and 0.413 N/mm^2^ vs. 1.160 and 1.059 N/mm^2^). Also mean values of maximum and minimum COF are lower for the Pulsar-18 compared to the LifeStent (0.313 and 0.249 N/mm^2^ vs. 0.732 and 0.575 N/mm^2^). The strut dimensions of the Pulsar-18 are 139 × 90 μm compared to 192 × 102 μm for the LifeStent.

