### Primary endpoint

Primary endpoint is the amount of in-stent neointima at 1 year, assessed by contrast-enhanced CT angiography (CTA). The volume of neointima inside the stent will be calculated by measuring every 2 mm along the longitudinal axis of the stent: (i) the diameter of the stent in two perpendicular directions and (ii) the diameter of the contrast-enhanced lumen in two perpendicular directions. The difference between these two measurements represents the thickness of the neointima, which will be represented relative to (as percentage of) the stent diameter.

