### Procedure

Vascular access is performed at the investigators discretion under local anesthesia, sedation, or general anesthesia. A contralateral or ipsilateral approach is permissible. A bolus of 5000 units of heparin is administered i.v. Diagnostic angiography is performed from the groin to the ankle (from the aortic bifurcation if no non-invasive imaging is available to document the patency of the inflow). Endovascular treatment of stenosed inflow (including the SFA orifice) and (after successful index lesion transversal) outflow lesions is permissible.

After successful lesion transversal and confirmation of inflow and outflow patency, the patient will be randomized one-to-one by a clinical research assistant (CRA). For this purpose, an online randomization program (www.sealedenvelope.com) will be used to generate a random 1:1 group allocation (block randomization). Only one limb is eligible for inclusion in the study.

A radiopaque calibrated ruler will be present on all radiographic images. Diameter measurements of the proximal and distal landing zone in a un-diseased SFA segment will be performed. These measurements will be used to select the balloon size for pre- and post-dilatation as well as the stent size according to the manufacturers’ stent-sizing table. After pre-dilatation with a subdiameter PTA balloon for 1 minute, the stent will be deployed and the post-dilated. The diameters for the pre- and post-dilatation balloon and the stent diameter will be determined after measuring the diameter of the non-diseased SFA at the proximal end of the intended treatment site. Table 1 gives the respective diameters of the stents for different SFA diameter ranges.

Stents will be deployed beginning with the most distal site. Spot-stenting of multiple lesions is permissible. Any balloon pre-dilated lesion should be covered by the device. Incomplete covered areas, if present, will be evaluated separately.

Stents will be assessed for correct implantation length by observing the relative proximal and distal stent markers with the corresponding delivery system markers. Deviations will be recorded as millimeter elongation or compression.

Completion angiography will be performed from the groin to the ankle (aortic bifurcation to ankle if inflow lesion treatment has been performed). After confirmation of absence of relevant residual stenosis the wire will be removed and radiography of the stent will be performed in two planes differing by ≥ 30 degrees.

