### Statistical analysis

Sample size calculation is based on the primary endpoint at 1 and 2 years represented by the percentage of in-stent neointima formation (relative to the stent diameter). Statistical significance between the groups will be tested using a *t* test at a level of significance of 0.05. To detect a difference of 0.8 standard deviations with a statistical power of 90%, a sample size of 34 patients in each group is required. With a maximum dropout rate of 15%, 40 patients will be randomized per group.

A two-sided *t* test will be used to compare amount of neointima between the two treatment groups. In case of non-normally distributed data, appropriate normalizing transformations will be applied. To evaluate the degree of association between the extent of chronic outward force (by using the data presented in Fig. 4 showing COF of stent fabricates according to stent diameter) and the amount of in-stent neointima, a linear regression analysis will be performed independently of the stent allocation group. Primarily, analysis will be based on intention-to-treat. If protocol deviations occur, the analysis will be performed both on an intention-to-treat and on a per protocol basis.

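### High local COF coinciding with high neointima does not show direct activation: COF is read from local stent diameter, which residual stenosis reduces, and neointima is scaled by local stent diameter

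*Protocol article*

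**What the plan says.** All references are to the protocol article.

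- **How COF is obtained.** COF is not measured in the patient. Stent diameter is read every 2 mm on the completion angiogram (Procedure) and converted with bench-test curves (Stent types, text at Fig. 4): "Using these curves, the COF of each stent can be determined for every diameter below its nominal diameter".
- **How neointima is scaled.** The primary endpoint is the difference between stent and lumen diameter, "which will be represented relative to (as percentage of) the stent diameter". The CTA section gives the same quantity as a formula with the stent diameter in the denominator.
- **Planned regression.** Under Statistical analysis, COF is related to neointima, and "a linear regression analysis will be performed independently of the stent allocation group".
- **Local comparison.** The Discussion says that "in-group and in-patient correlations of COF and neointima are possible in post hoc evaluations". It explains that COF is locally higher "in places where some residual stenosis leads to higher compression of the stent and thus to higher chronic outward force", and low where the stent is close to its nominal diameter.
- **Inference.** The same paragraph then states: "If neointima formation is highest at the very same location as high COF, a direct activation of muscle cell proliferation may be assumed". Neointima lying downstream of high COF is taken to point to humoral or paracrine stimulation instead.
- **Residual stenosis at completion.** The Procedure section requires only that: "After confirmation of absence of relevant residual stenosis the wire will be removed". Lesser degrees can remain.

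**The concern.** The paragraph names a common antecedent and then reasons as if there were none. Within one stent, a high-COF site is by construction an under-expanded site, and the article itself attributes under-expansion to residual stenosis. If the diseased segment re-narrows more for reasons of its own, high COF and high neointima will coincide even when force does nothing. Randomisation assigns patients to stents, not sites to levels of COF, so it gives no protection here.

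A second route needs no biology. COF rises as local stent diameter falls, and percentage restenosis is divided by local stent diameter. The two are therefore coupled through a shared quantity.

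What is at stake is the mechanistic conclusion. The arms differ in stent make, strut dimensions and degree of oversizing, so the association of neointima with COF is the evidence that would tie a difference between arms to force rather than to the product. As worded, a pattern expected with no COF effect would be read as direct activation.

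**Working it through.** **1. The plan's own figure.** A two-sided t test, 0.8 SD, alpha 0.05 and 90% power give 33.83, rounded up to 34 per group (power 0.9015 at 34). Also 34 / 0.85 = 40. The stated sample size reproduces, and this point does not touch it.

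**2. The scale, with no COF effect.** The formulas are the article's:
- % oversizing = (Dn − d) / Dn × 100 (Procedure)
- % restenosis = (Ds − dl) / Ds × 100 (CTA)

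Take Dn = 6 mm. Hold the absolute difference Ds − dl constant (assumed), and let the stent diameter at CTA equal that at completion (assumed).

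| Stent diameter (mm) | % oversizing | % restenosis, 0.5 mm | 1.0 mm | 1.5 mm |
|---|---|---|---|---|
| 5.5 | 8.3 | 9.1 | 18.2 | 27.3 |
| 5.0 | 16.7 | 10.0 | 20.0 | 30.0 |
| 4.5 | 25.0 | 11.1 | 22.2 | 33.3 |
| 4.0 | 33.3 | 12.5 | 25.0 | 37.5 |
| 3.5 | 41.7 | 14.3 | 28.6 | 42.9 |

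Whatever the constant thickness, the percentage rises by the factor 5.5 / 3.5 = 1.57 from the widest to the narrowest site.

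**3. Within-stent simulation, zero COF effect.** Assumed: 50 levels per stent, diameter 5.0 mm (SD 0.4), stent-minus-lumen difference 1.0 mm (SD 0.3), and % oversizing in place of COF. By chance alone, the peak would fall in the top COF quartile in about 25% of stents.

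| Assumed correlation of local lesion with absolute neointima | Mean COF correlation, absolute | Mean COF correlation, percentage | Peak % restenosis in top COF quartile |
|---|---|---|---|
| 0 | 0.00 | 0.25 | 60% |
| 0.2 | 0.20 | 0.43 | 74% |
| 0.3 | 0.30 | 0.51 | 81% |
| 0.5 | 0.50 | 0.66 | 91% |

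The first row is the scale effect alone, and it vanishes on the absolute scale. The other rows add the assumed lesion effect, which remains on the absolute scale. Each route therefore needs its own remedy.

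**4. The pooled regression.** Here allocation itself creates much of the COF variation. From the Stent types figures, the midpoints are (0.732 + 0.575) / 2 = 0.654 and (0.313 + 0.249) / 2 = 0.281 N/mm², a gap of about 0.37. The simulation used 34 patients per arm, no COF effect, and lesion severity correlated r with neointima and, within arm, with COF. The article gives neither r nor the within-arm SD of COF, so both are assumed. Entries are the percentage of trials with a significant COF slope at 0.05.

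| r | SD 0.05 | SD 0.10 | SD 0.20 | No gap between arms |
|---|---|---|---|---|
| 0.3 | 5.5 | 6.4 | 8.0 | 11.5 |
| 0.4 | 6.3 | 9.0 | 15.6 | 25.8 |
| 0.5 | 8.1 | 15.6 | 32.2 | 54.2 |

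With severity as a covariate, the rate returns to about 5%. That supposes severity is measured without error. In the no-gap case at r = 0.4, an assumed reliability of 0.6 to 0.8 brings it down only to about 9% to 6%.

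**The case against.** The strongest reply is that nothing is fixed. The sentence stands in the Discussion, concerns optional post hoc work, and is hedged; no endpoint or test depends on it. That is correct and limits the weight of the point. It does not make the inference sound: the article offers a reading of co-location and mentions neither the lesion nor the scale as an alternative.

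Second, the lesion route rests on a premise outside the document. The article speaks only of some residual stenosis. It does not say that such sites are the original lesion core, carry the most plaque, take the most dilatation injury, or form more neointima independently of force. Pre- and post-dilatation, the completion check and the exclusion of severe calcification that impedes pre-dilatation all reduce the pathway. This stands, and the lesion effect is treated here as an assumption. The scale route does not need it.

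Third, a reader might infer that the planned regression is badly confounded, with false positives of about 25% at r = 0.4 or 54% at r = 0.5. Those rates arise only if COF is simulated without the two randomised arms, so the documents do not support them as a description of this regression. Nor is the absence of named covariates a defect in itself: the adjustment set may be in the full protocol or the analysis plan, which are not shown.

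**Conclusion.** The point holds as a limit on interpretation. Post hoc co-location of high COF and high neointima cannot, as described, distinguish an effect of force from an effect of the local lesion. On the percentage scale it is expected even when neither acts.

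- **Scale effect:** 18.2% to 28.6% between stent diameters of 5.5 and 3.5 mm, for a 6 mm stent and a constant 1.0 mm difference. It requires that absolute thickness does not shrink in proportion to diameter and that the diameter at CTA follows the completion diameter.
- **Lesion effect:** its size is unknown, because the documents do not say that residual lesion promotes neointima.
- **Pooled regression:** a false-positive rate of about 6% to 16% at r = 0.4, for assumed within-arm COF SDs of 0.05 to 0.20 N/mm². It would be larger only if both the correlation and the within-arm spread were high.

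A reader might go further and infer that the trial's main result is compromised. It is not: the primary comparison is between randomised arms, and its t test and sample size are untouched.

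**What to change.** 1. In the level-wise COF-neointima analyses, adjust for pre-treatment lesion status at the matching stent position. Use either % stenosis or the categories occluded, stenosed and landing zone, read from the diagnostic angiogram. The calibrated ruler is already on all radiographic images. The categories also cover complete occlusions.
2. Run the pooled COF regression with the same adjustment as a sensitivity analysis.
3. In both, report absolute neointimal thickness beside the percentage of stent diameter.
4. Replace the sentence in the Discussion with wording such as: co-location of high COF and high neointima is hypothesis-generating; it supports a direct effect of COF only if it persists after adjustment for pre-treatment lesion status and on the absolute scale.

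The cost is some extra readings on images already taken, one covariate and a reworded sentence. The adjusted COF estimate will be less precise, and error in the lesion readings will leave some confounding. Enrolment, treatment and the primary endpoint do not change.

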## Trial status

Recruitment has started in October 2015 and is estimated to be completed in December 2017.

## Abbreviations

ABI: Ankle-brachial index
CDUS: Color-flow Doppler ultrasound
COF: Chronic outward force
CRA: Clinical research assistant
CTA: CT angiography
RRF: Radial resistive force
SFA: Superficial femoral artery
TLR: Target lesion revascularization
